#### 10.6.4. Follow-up of Adverse Events

The Principal Investigator must continuously follow up on all collected adverse events until they are resolved or stable. Serious adverse events that have not resolved by the time a subject completes the study (at their last visit or date of discontinuation) must be followed up until one of the following occurs.

- The serious adverse event resolves or stabilizes (as per the investigator's clinical judgment).
- Abnormal clinical test values return to the normal range or baseline.
- The subject dies.
- Follow-up becomes impossible (e.g., loss of contact).

If a study must be prematurely terminated due to an adverse event, an adverse event report must be created and a final laboratory test conducted.

If a follow-up of a subject is impossible before an adverse event resolves/stabilizes or its cause is determined, the Principal Investigator must make every effort to contact the subject and collect information. This must also be documented.

#### 10.6.5. Reporting of Adverse Events

During the study, the Principal and Sub-investigators must ensure the safety of the subjects. In the event of a serious adverse event, they must take swift and appropriate action.

In the event of a serious adverse event, the responsibilities of each person in charge are as follows:

### 1) Sub-Investigators

The sub-investigator must report all serious adverse events that occur during the study to the Principal Investigator within 24 hours, regardless of their relationship to the investigational product. Any other events considered serious by the sub-investigator or that suggest a significant risk, contraindication, side effect, or precaution related to the medication must also be recorded as a serious adverse event in the CRF.

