### 10.6.2. Definition of Serious Adverse Events

Serious Adverse Event / Adverse Drug Reaction (Serious AE/ADR) is an adverse event or adverse drug reaction occurring at any dose of an investigational product that leads to any of the following outcomes

- Death or life-threatening situation.
- Requires or prolongs hospitalization.
- Results in persistent or significant disability/incapacity.
- Causes a congenital anomaly or birth defect in an offspring.
- Other medically significant events, such as drug dependency or abuse, or hematological disorders, that are not listed above.

However, the following are not considered Serious AEs/ADRs

- Hospitalization for a simple observation or examination with no treatment.
- Subject's elective surgery or a pre-planned surgery for an existing condition.

Suspected Unexpected Serious Adverse Reaction (SUSAR) is any serious, unexpected, and suspected

adverse drug reaction that occurs during the use of an investigational product. It must meet all three of the following criteria

- Suspected adverse drug reaction
- Serious
- Unexpected

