- 5) Autonomic Nervous System: May cause insomnia, excessive sweating, tachycardia, frequent urination, palpitations, systemic weakness, mental agitation, etc.
- 6) Urinary System: May cause micturition disorders.

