For the assessment and reporting of a SUSAR, unblinding must be performed as necessary in accordance with the ICH E2A guideline, as long as it does not affect the conduct or outcome of the clinical trial.

However, if an adverse drug reaction results in death, unblinding must be performed to confirm the type of suspected drug, and this information must be included in the SUSAR report.

A SUSAR report that has been unblinded must not be provided to or exposed to the blind team.

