### **11.3. Statistical Analysis of Safety Assessment**

The safety evaluation will analyze the frequency of adverse events and serious adverse events suspected to be related to the treatment. Adverse events will be collected through subject reports or investigator observations. The reported adverse events will be described narratively, and the frequencies of events related and unrelated to the study intervention will be recorded and presented using descriptive statistics. The event count per visit between the groups will be compared using Fisher's exact test. The pre- and post-treatment values for each laboratory test variable will be analyzed using a paired t-test to determine if there is a difference.

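### Section 10.6.5(1) adds a drug-signal route to serious coding that 10.6.2 does not contain, so the serious-event count and the duties tied to it are ambiguous

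*Protocol*

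**What the plan says.** Protocol 10.6.2 treats an adverse event or reaction as serious when it is one "occurring at any dose of an investigational product that leads to any of the following outcomes". The list covers death or threat to life, hospital admission or a longer stay, disability, and birth defect. It closes with an open item: "Other medically significant events, such as drug dependency or abuse, or hematological disorders, that are not listed above".

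Protocol 10.6.5, item 1 (Sub-Investigators), first requires every serious adverse event to reach the Principal Investigator within 24 hours, whatever its relation to the product. It then widens the class. The sentence begins "Any other events considered serious by the sub-investigator or that" and continues "suggest a significant risk, contraindication, side effect, or precaution related to the medication must also be recorded as a serious adverse event", with the CRF named as the place of entry.

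The safety analysis in 11.3 "will analyze the frequency of adverse events and serious adverse events suspected to be related to the treatment". Item 2 of 10.6.5 attaches further duties to serious status: 24-hour notice to the monitor, a report to the IRB, a written follow-up report within 10 days, and suspension of all or part of the trial.

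**The concern.** Seriousness and suspected relation to the drug are separate attributes of an event, and most of this protocol keeps them apart. The second part of the 10.6.5(1) sentence turns the second attribute into the first. An event that meets nothing in 10.6.2, and that nobody judges serious, must still be entered as serious if it suggests a significant side effect or precaution of the medication.

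Two things are at stake. The serious-event frequency in 11.3 could mix events that meet 10.6.2 with reactions that do not, in proportions that depend on which section a site follows. The notification and suspension duties in 10.6.5(2) could also be triggered by events outside the definition. Coding happens at the site during data capture, so an analysis plan cannot easily undo it later.

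**Working it through.** No figure in the protocol bears on this point, so the check compares the texts. A short illustration of size follows.

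**1. What sets the added class apart.** The preceding sentence already deals with all serious adverse events. The next one speaks of *other* events, which places them outside that set. Within it, *or* separates events the sub-investigator considers serious from events that suggest a drug-related signal. The second group therefore needs neither a 10.6.2 outcome nor a judgement of seriousness. The instruction is mandatory and names the CRF, so it governs data and not only early warning.

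**2. The two sections applied to example events.**

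| Event | Serious under 10.6.2? | Serious under 10.6.5? |
|---|---|---|
| Admission to treat a drug reaction | Yes | Yes |
| Haematological disorder without admission | Yes, open item | Yes |
| Marked palpitations thought drug-related, no admission, not judged serious or medically important | No | Arguably yes, as a significant side effect |
| Mild itching thought drug-related | No | Only if *significant* qualifies the risk alone and not the whole list |
| Admission for treatment, plainly unrelated to the product | Yes | No, excluded by item 2 |

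The third and fourth rows are the conflict. They are not far-fetched. Section 10.6.3 lists predictable GGTCS reactions for skin and gut, and for the autonomic system states "May cause insomnia, excessive sweating, tachycardia, frequent urination, palpitations, systemic weakness, mental agitation, etc". The last row is a second mismatch, running the other way. Item 2 of 10.6.5 removes unrelated admissions from the serious class. Section 10.6.2 has no such exclusion, and item 1 asks for serious events regardless of relation.

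**3. Where these events would otherwise go.** Section 10.6.1 already defines an adverse drug reaction by a causal link that cannot be ruled out, and 10.6.3 grades severity and causality. The SUSAR rule in 10.6.2 lists suspected, serious and unexpected as three separate conditions. The drug-signal class thus has a place in the protocol without the serious label.

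**4. Where serious status is used.** It feeds the frequency in 11.3 and the notification, IRB, written-report and suspension duties in 10.6.5(2). It is also one of the three SUSAR conditions, and 10.6.5(2) adds: "For the assessment and reporting of a SUSAR, unblinding must be performed as necessary".

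**5. Size.** The protocol gives no adverse-event or serious-event rate for either arm. To show what is undetermined, assume rates of subjects coded serious by the added route, with the 88 per group of section 5.3. Count = 88 × rate, rounded; p is from Fisher's exact test, two-sided.

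| Assumed GGTCS rate | Assumed placebo rate | Counts | p |
|---|---|---|---|
| 2% | 5% | 2 vs 4 | 0.68 |
| 5% | 5% | 4 vs 4 | 1.0 |
| 10% | 5% | 9 vs 4 | 0.25 |
| 10% | 2% | 9 vs 2 | 0.057 |
| 15% | 2% | 13 vs 2 | 0.005 |

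For example, 88 × 0.10 = 8.8, rounded to 9, and 88 × 0.02 = 1.76, rounded to 2. The picture runs from no imbalance to a marked one and follows entirely from the assumed rates. The table is not a forecast.

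**The case against.** The best defence is that the clause is a cautious catch-all. *Significant* can be read across the whole list, the sentence sits under duties for serious events, and 10.6.2 itself ends with an open item. On that reading a mild case of an already listed reaction would hardly qualify. This stands in part: it narrows the added class and makes the conflict one about the edge of an open category. It does not remove the conflict, because a significant side effect or precaution is still a statement about the drug, and not every such event is medically important in the sense of 10.6.2.

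A reader might infer more than the text supports, in three ways.

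- *That the extra events would fall mainly in the GGTCS arm.* The list of predictable reactions makes this plausible, but no rates are given. Section 6.4 blinds investigators, so a site's reading applies to both its arms. A real excess of reactions would also appear in ordinary adverse-event reporting.
- *That mild unlisted reactions become SUSARs and lead to unblinding.* The SUSAR conditions stand inside 10.6.2, directly below the definition of serious, so that definition is the natural one to apply. Unblinding is limited to what is necessary, subject to not affecting the trial's conduct or outcome (with a separate rule for deaths), and unblinded reports are kept from the blinded team.
- *That a formal comparison of serious events is corrupted.* The Fisher test in 11.3 is on events per visit, not on serious events specifically, and narratives could reveal a mild event carrying a serious label. The trial-level stopping criterion in 7.2 uses severity and relatedness, not seriousness.

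**Conclusion.** The concern holds as an inconsistency between 10.6.5(1) and 10.6.2. The protocol contains a mandatory route to serious coding that its definition does not contain and that overlaps only partly with the open item. Some non-serious drug reactions may be coded as serious, and three sites may not code alike. The serious-event frequency in 11.3 and the duties in 10.6.5(2) are therefore ambiguous.

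This is a risk under the written wording, not a certainty, and it is smaller if *significant* is taken to govern the whole list. The size and direction of any between-arm effect cannot be determined from the document. The primary efficacy analysis is not affected. It should be corrected, because the ambiguity enters at data capture and the correction is cheap.

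**What to change.** Reconcile 10.6.5 with 10.6.2 so that one definition of serious governs CRF coding, the serious-event frequency in 11.3 and the SUSAR test.

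- Keep the sub-investigator's own judgement of seriousness, placed under the open item for medically important events, so that aligning the sections does not delete it.
- Record other events that suggest a drug-related risk as adverse events or adverse drug reactions, with severity and causality, and add a separate CRF flag that prompts early notice to the Principal Investigator. They stay out of the serious-event count unless they meet the definition.
- Reconcile at the same time the 10.6.5(2) exclusion of admissions unrelated to the product, which 10.6.2 lacks.
- State which class of events the notification and suspension duties in 10.6.5(2) refer to. The content of those duties is for the sponsor and investigators.

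The cost is a small amendment, one CRF field and a re-briefing of the sites. Early warning of drug signals is kept.

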### 2) Principal Investigator

The Principal Investigator must verbally or by email notify the assigned monitor at the Korea Institute of Oriental Medicine within 24 hours of becoming aware of any serious adverse event, in accordance with the Clinical Trial Management Guidelines. They must also report it to the Institutional Review Board (IRB) within the period set by the IRB.

Furthermore, a detailed written follow-up report must be submitted within 10 days of the serious adverse event's occurrence. In this case, to protect the confidentiality of the subject's personal information, the Principal Investigator must use a subject identification code instead of the subject's name, resident registration number, and address. The Principal Investigator must also suspend all or part of the clinical trial until further notice.

The following are not considered a serious adverse event:

- Hospitalization that is clearly unrelated to the investigational product.
- Hospitalization for simple observation or examination with no treatment.

In the event of a Suspected Unexpected Serious Adverse Reaction (SUSAR), the Principal Investigator must report it through the electronic reporting system for clinical trial adverse drug reactions on the MFDS e-civil application website (<http://ezdrug.mfds.go.kr>) within the deadlines stipulated by the Clinical Trial Management Guidelines.

- Events resulting in death or that are life-threatening: Within 7 days of the Principal Investigator receiving or becoming aware of the fact. However, if all information required by Form 77, such as the adverse drug reaction name, final observation results, and a summary of the adverse drug reaction, has not been reported, the Principal Investigator must submit an additional report with detailed information within 15 days of first receiving or becoming aware of the adverse drug reaction.
- Other serious and unexpected adverse drug reactions: Within 15 days of the Principal Investigator receiving or becoming aware of the fact.

When reporting an adverse drug reaction to the Minister of Food and Drug Safety, the principal

investigator must attach a summary of the adverse drug reaction, such as a CIOMS-I form, to the adverse drug reaction report. The investigator must also periodically report additional safety information until the adverse drug reaction is resolved (disappears or further follow-up is not possible).

For the assessment and reporting of a SUSAR, unblinding must be performed as necessary in accordance with the ICH E2A guideline, as long as it does not affect the conduct or outcome of the clinical trial.

However, if an adverse drug reaction results in death, unblinding must be performed to confirm the type of suspected drug, and this information must be included in the SUSAR report.

A SUSAR report that has been unblinded must not be provided to or exposed to the blind team.

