## 10.6. Adverse Events and Serious Adverse Events

### 10.6.1. Definition of Adverse Events

Adverse Event (AE) is any untoward and unintended sign (including abnormal laboratory findings), symptom, or disease that occurs in a subject administered an investigational product, and it does not necessarily have a causal relationship with the investigational product.

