#### 2) Causality Assessment of the Investigational Product

When an adverse event occurs, the investigator will assess its causal relationship with the investigational product based on the following criteria and provide their opinion if necessary.

A causal relationship with an investigational product cannot be statistically tested, so it is determined by considering individual circumstances, medical plausibility (physiological, pathological, pharmacological), and literature. Considering the temporal relationship is also helpful. Additionally, the investigator will consider whether the event disappeared upon discontinuation and reappeared upon re-administration of the drug, as well as any concomitant therapies or medications.

The certainty of the relationship between the adverse event and the investigational product (or other causes, such as underlying disease progression or concomitant treatment) is determined by how well the adverse event can be explained in terms of the following

- ① Known pharmacological actions of the investigational product.
- ② Similar actions previously observed with the investigational product or a drug of the same class.
- ③ Reactions frequently reported in relation to similar drugs.
- ④ A reaction that is temporally related to drug administration (disappears upon drug

discontinuation and reappears upon re-administration).

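### Protocol section 10.6.5(2) removes clearly unrelated hospitalisations from the serious adverse events, against the outcome-based definition in 10.6.2

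*Protocol*

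**What the plan says.** Section 10.6.2 of the Protocol defines an SAE as an adverse event or adverse drug reaction with one of several listed outcomes. One of these is "Requires or prolongs hospitalization". It then gives two exceptions. One covers admission only for observation or tests, without treatment. The other covers "elective surgery or a pre-planned surgery for an existing condition". Neither refers to the cause of the event.

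Section 10.6.1 says of an adverse event in general that "it does not necessarily have a causal relationship with the investigational product".

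Section 10.6.5, item 1, has sub-investigators report all SAEs to the Principal Investigator within 24 hours, "regardless of their relationship to the investigational product".

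Section 10.6.5, item 2, has the Principal Investigator notify the monitor "within 24 hours of becoming aware of any serious adverse event", report to the IRB within the IRB's own period, and send a detailed written report within 10 days of the event. It then gives its own two-item list of what is not an SAE. One item repeats the observation exception. The other is "Hospitalization that is clearly unrelated to the investigational product".

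**The concern.** Whether an event is serious and whether the product caused it are separate questions, and section 10.6.2 keeps them apart by judging seriousness on outcome alone. The bullet in 10.6.5(2) joins them, so that an opinion on cause decides whether an admission is serious at all.

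That opinion is a matter of judgement. Section 10.6.3 states: "A causal relationship with an investigational product cannot be statistically tested, so it is determined by considering individual circumstances". At stake are the reports that bring an admission to people outside the investigator's team. If the investigator judges the admission clearly unrelated and follows 10.6.5(2), the monitor and the IRB may not hear of it through the SAE route and so have no prompt to question the judgement.

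**Working it through.** The contradiction rests on text, and the plan gives no figure to reproduce. Take one test case: a subject is admitted and treated during the trial, the investigator judges the cause clearly unrelated to the product, and no seriousness criterion other than hospitalisation is met.

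| Protocol section | Basis for the decision | Result for the test case |
|---|---|---|
| 10.6.1 | Untoward event in a treated subject, no causal link needed | Adverse event |
| 10.6.2 | Outcome: hospitalisation; neither exception applies | Serious |
| 10.6.5(1) | SAEs reported whatever the relationship | To the Principal Investigator within 24 hours |
| 10.6.5(2) | Causality: clearly unrelated | Not serious |

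The second and fourth rows cannot both hold. This is the direct contradiction. Row three is undercut in effect: the sub-investigator passes the event up as an SAE whatever its cause, and the next item then withdraws that status because of its cause. Row one is background. It confirms that an unrelated event is still an adverse event and so falls within 10.6.2, but it says nothing about seriousness and is not itself contradicted.

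**Consequences if a site follows 10.6.5(2)**

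- Could be lost: the 24-hour notice to the monitor, the IRB report and the 10-day written report, all of which attach to SAEs.
- Kept: follow-up of all collected adverse events until resolved or stable (10.6.4).
- Kept: presentation of event frequencies both related and unrelated to the intervention (11.3).
- Kept: SUSAR reporting, which requires a suspected reaction (10.6.2) and so never applied to an event judged unrelated.
- Not touched: any efficacy endpoint or analysis.

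**How often this could arise**

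The Protocol gives no hospitalisation rate. It does fix the observation time: adverse events are monitored from first administration (10.6.1), Visit 3 falls on Day 7 to 10, and 176 subjects are planned (5.3).

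- Person-years at 7 days: 176 × 7 / 365 = 3.38.
- Person-years at 10 days: 176 × 10 / 365 = 4.82.
- Annual rate of unrelated, treated admissions at which one event would be expected: 1 / 4.82 = 0.21 at 10 days and 1 / 3.38 = 0.30 at 7 days.

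One event would therefore be expected only at a rate of about 21% to 30% per year. As a pure assumption, with no anchor in the documents, 2% per year over 7 days gives 0.02 × 3.38 = 0.07 expected events, and 10% per year over 10 days gives 0.10 × 4.82 = 0.48. The contradiction itself depends on none of these numbers.

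**The case against.** The strongest defence is that the list in 10.6.5(2) only narrows the Principal Investigator's expedited reporting. It fails on the wording: the list says these events are not SAEs, and the duty it follows covers any SAE.

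Several limiting points do stand, and they block stronger readings that a reader might infer:

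- **Three separate contradictions.** Only 10.6.2 is directly contradicted. Section 10.6.5(1) is undercut in effect, and 10.6.1 does not address seriousness.
- **Reports will be missed.** The documents support only that they could be. A site may follow the definition section instead. The Principal Investigator's notice is also tied to outside trial-management guidelines that are not at hand. Section 10.6.5(1) further has other events that the sub-investigator considers serious recorded as SAEs in the CRF.
- **All unrelated serious events drop out.** The bullet speaks only of hospitalisation. An unrelated event that is fatal, life-threatening, disabling or otherwise medically significant still meets another criterion in 10.6.2.
- **The elective-surgery exception is lost.** It is missing from the 10.6.5(2) list, but 10.6.2 still applies and already removes such surgery from SAE status. The omission is harmless.
- **The term is undefined.** It lies close to the category in 10.6.3 for events definitely not related. The fault is the use of a causality opinion to settle seriousness, not vagueness.

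**Conclusion.** The Protocol is wrong as written on this point. Section 10.6.5(2) denies SAE status to an admission that 10.6.2 calls serious, and the only ground for the difference is a judgement on cause. The effect is confined to three reports on a narrow class of events: treated admissions judged clearly unrelated that meet no other seriousness criterion.

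Severity is minor. The judgement that few such events will occur rests on the planned 176 subjects and the 7 to 10 days of observation; the admission rate itself is unknown from the documents. That the reports could be lost assumes a site follows 10.6.5(2) rather than 10.6.2.

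**What to change.** Delete the bullet on clearly unrelated hospitalisation from 10.6.5(2), or replace the two-item list there with a reference to the exceptions in 10.6.2. The second option is tidier, because it leaves one list of exceptions in the Protocol. Causality would then matter for classifying adverse drug reactions and SUSARs, and not for seriousness.

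The cost is one small protocol amendment and at most a few more SAE reports, with no new visit, test or procedure.

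One side effect should be known beforehand. Section 10.6.5(2) also states: "The Principal Investigator must also suspend all or part of the clinical trial until further notice". Once the bullet is gone, that sentence would cover these admissions too, as it already covers every other SAE. Whether it should be reworded is a separate matter and not part of this correction.
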